## Abstract

**Background:**

Traumatic brain injury (TBI) is one of the most important pediatric conditions worldwide. In Germany, hospitalization rates for mild TBI drastically exceed hospitalization rates from similar healthcare systems.

**Methods:**

The SaVeBRAIN.Kids trial will implement and test a novel care pathway (nCP) for evidence-based standardized risk assessment, structured observation in the emergency department (ED) for several hours, and technology-supported home monitoring with the aim to reduce hospitalizations. This non-inferiority multicenter study will be carried out using a cluster-randomized stepped-wedge design, with all centers starting in the control phase and sequentially transitioning to the intervention. Eligible participants (age ≥ 3 months and < 18 years) must present within 48 h of head injury, have minimal symptoms (Glasgow coma scale ≥ 14), and no risk factors for intracranial complications. The co-primary outcomes are the relative risk of hospitalization and the proportion of unplanned re-visits within 72 h of presentation to the ED for ambulatory cases. Secondary outcomes include clinical safety measures, cost-effectiveness, and process evaluation. Based on power calculations (*α* = 0.05, power = 0.9), 1390 patients will be recruited over 12 months.

**Discussion:**

The SaVeBRAIN.Kids trial addresses a relevant healthcare challenge by testing a new approach to pediatric mild TBI management in Germany. It aligns with current evidence while accounting for the country’s specific healthcare context. If successful, the intervention could substantially reduce unnecessary hospitalizations and free inpatient capacities while preserving patient safety.

**Trial registration:**

German Clinical Trials Registry (DRKS00035623). Registered on January 21, 2025.

**Supplementary Information:**

The online version contains supplementary material available at 10.1186/s13063-025-09240-8.

## Introduction

Traumatic brain injury (TBI) is defined as the presence of neurological symptoms indicating brain dysfunction and/or injury to the brain, skull bones, or adjacent structures resulting from mechanical force on the head [1]. Symptoms range from mild headaches to deep unconsciousness and can occur isolated or as complex symptom patterns. Based on the presence/extent of initial state of consciousness, TBI is classified into three severity grades: mild, moderate, or severe, with mild TBI (mTBI) significantly dominating pediatric cases at 97%.

In Germany and worldwide, TBI represents one of the most epidemiologically and health-economically relevant pediatric conditions, accounting for approximately 92,000 pediatric hospital admissions per year in Germany. Of these, approximately 2500 (2.7%) are diagnosed with imaging-confirmed intracranial injury/complications, and only about 600 (0.7%) require neurosurgical intervention [2]. Notably, Germany’s pediatric TBI hospitalization rate of 687/100,000 child-years (CY) (1457/100,000 CY for infants) is the highest reported in literature worldwide [2]. In contrast, the UK reports 280/100,000 CY [3], and the USA merely 73/100,000 CY [4].

The high hospitalization rates in Germany are likely attributable to insufficiently standardized local care pathways for mild TBI, resulting in clinical uncertainty during decision-making among healthcare providers. The current German national guideline for “TBI in Childhood and Adolescence” broadly recommends inpatient monitoring, particularly for children under 2 years of age. Vague recommendations regarding difficult-to-objectify symptoms like mild or transient consciousness impairment, headaches, nausea, or dizziness add up with lacking options to monitor the short-term clinical course in the emergency department.

As a result, inpatient observation is often carried out despite lacking medical necessity. Further, the median duration hospital stay of 2 days for children with mild TBI exceeds the guideline-specified timeframe for intracranial complication manifestation (6–12 h). Contrasting the German practice, the USA guideline recommends no monitoring for patients at low risk for intracranial complications, while guidelines in the UK, Scandinavia, and the Netherlands recommend only hourly monitoring in a clinical setting for these patients [5–8].

The SaVeBRAIN.Kids trial will evaluate a novel care pathway (nCP) for children with mTBI that was designed to (1) standardize management of mild TBI; (2) implement the option of a short-term symptom-oriented observation in the emergency department (ED) instead of immediate hospital admission; (3) support caregivers during home monitoring via a specifically designed smart phone app. The aim of the nCP is to reduce the proportion of hospitalizations among pediatric patients with mTBI, who are at very low risk for relevant intracranial complications while maintaining equivalent medical safety to the current standard of care. The study will be carried out as a non-inferiority trial using a multi-centered cluster-randomized stepped-wedge design with the hospitalization rate and unplanned re-visits within 72 h from ED discharge as co-primary outcomes.

## Methods

### Participants, interventions, and outcomes

#### Study setting

Eleven pediatric study sites in Germany will participate in the study, including university hospitals, non-university tertiary care centers, and community hospitals from across the country (Fig. 1). Eleven study sites were recruited on a first-come-first-serve basis. Individuals performing the intervention at the study sites will be local investigators that oversee the local ED staff (physicians and nurses).

**Fig. 1 Fig1:**
[figure not shown]
SaVeBRAIN.Kids study sites

#### Eligibility criteria

Admission to the nCP requires a strict pre-selection of patients with a very low risk of clinically relevant intracranial complications. The risk assessment for a clinically relevant intracranial injury is based on the Glasgow Coma Scale (GCS) and further evidence-based clinical risk factors that are suitable to identify children with intracranial injuries [9]. The clinical factors chosen for SaVeBRAIN.Kids are based on the symptoms defined in the PECARN rule (Pediatric Emergency Care Applied Research Network (PECARN) Head Injury Decision Rule) and the German guideline [1, 10], as well as the clinical course during the monitoring period.

Key eligibility criteria are age ≥ 3 months and < 18 years, head trauma or mild TBI within ≤ 48 h of presentation to the ED, and the absence of risk factors (Table 1).

**Table 1 Tab1:** Inclusion and exclusion criteria, mandatory monitoring, and inpatient admission requirements for pediatric patients with mild traumatic brain injury (TBI) in the emergency department

**Inclusion criteria**	• Age ≥ 3 months and < 18 years, who have an ICD-10 code of S06.0, S06.8, S06.9, or S02.0 • Head injury caused by direct or indirect mechanical force • At least one neurological symptom related to the head injury was/is present and/or there is a simple skull vault fracture • GCS ≥ 14 upon arrival in the emergency department • The structured medical history and examination reveal no increased risk or indication of a clinically relevant intracranial complication • The trauma occurred ≤ 48 h ago • The legal guardians have sufficient German language skills for providing the medical history, understanding information about the mild traumatic brain injury, and using the parent app • A suitable device is available for the legal guardians to use the parent app
**Exclusion criteria**	• Unconsciousness > 30 min • Head injury in the context of high-impact trauma • Head injury due to an explosion (so-called blast injury) • Penetrating injury • Open traumatic brain injury (TBI) • Known bleeding tendency/indication of a coagulation disorder • Known severe internal, oncological, or hematological underlying condition associated with an increased risk of complications or bleeding • Known (developmental) neurological underlying condition • Difficulty in reliably assessing the neurological status of the patient • Presence of a shunt/valve in cases of known elevated intracranial pressure/hydrocephalus • Use of medications that impair blood coagulation • Indications of intoxication (alcohol/medication/drugs/other substances) • Indications of injury with suicidal intent • Indications of child abuse • Indication for hospital admission due to associated injuries or social/structural reasons • Occupational accident insurance case and private health insurance case, as these are excluded by the sponsor statutory health insurance members with the last digits 4 and 9
**Monitoring in ED mandatory**	• Initial high symptom burden in the anamnesis • Brief loss of consciousness (≤ 30 min) • Impaired consciousness, disorientation, or amnesia • Any neurological abnormalities in the detailed neurological examination ◦ Cervical spine: Spontaneous pain in the cervical spine/neck area, pain with movement, restriction of movement range, or pain upon palpation ◦ Cranial nerve abnormalities ◦ Abnormal spontaneous motor activity ◦ Coordination abnormalities in following test: Finger-to-nose test or age-appropriate grasping, arm holding test, diadochokinesis, finger opposition test, gait pattern, toe/heel walking, Romberg stance, one-leg stance, tightrope walking ◦ Muscle weakness in upper or lower extremities ◦ Abnormal muscle tone ◦ Pathological muscle reflexes (BSR, PSR, ASR)
**Inpatient admission mandatory**	• Parents feel unsure about going home • The parents’ app does not work on the smartphone • High burden of symptoms with no improvement or worsening during monitoring in the ED • Newly emerged pathological findings during monitoring in the ED • Medical concerns from the physician regarding discharge to home • Trauma-related relevant pathological findings in imaging

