##### Observation in the ED

The nCP consists of symptom-based clinical neuromonitoring for at least 6 h starting at ED arrival and includes the assessment of the Glasgow Coma Scale (GCS), pupillomotor function, and vital signs. The frequency and duration of the monitoring and additional measures depend on the patient’s health condition upon arrival at the ED and during monitoring (Table 1). Hospital admission, imaging, or surgery are possible at any time as indicated according to clinical findings and clinical practice guidelines. Patients that remain stable during the nCP will be discharged home if the physician and the legal guardians agree that the child is fully conscious (GCS = 15), behaves age-appropriately, and does not display newly developed symptoms or demonstrates any focal neurological deficits. Pre-existing symptoms, such as headaches or vomiting, must have remained stable (without worsening), show signs of improvement, or have resolved during the monitoring period. The legal guardians must feel confident in conducting home monitoring, and the parent app must function on their smartphone. Additionally, adequate medical care in case of emergency must be ensured through a functioning emergency response chain or by the guardians’ ability to arrive at the ED. Deviations from the recommended care pathway are possible at any time but will be documented along with the reason (Table 2).

**Table 2 Tab2:** Reasons for deviations from the study protocol, including logistical, technical, medical, and personal factors

**Deviations from study protocol**	• Logistical reasons • Technical reasons • Admission at parents’ request • Discharge against medical advice • Study termination by the parents • Medical concerns from the physician • Others (string)

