##### Primary outcomes

 1st Co-primary outcome: Relative risk of hospitalization among all included cases (outpatient and inpatient) at initial ED presentation.

2nd Co-primary outcome: Proportion of cases with unplanned re-visit within 72 h after discharge from the ED.

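### One exclusion criterion is worded as an indication for admission and has no stated boundary with the grounds on which an included child counts as hospitalized in the first co-primary outcome

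*Protocol article*

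**What the plan says.** The Primary outcomes section defines the first co-primary as "Relative risk of hospitalization among all included cases (outpatient and inpatient) at initial ED presentation". Whoever is not included is in neither the numerator nor the denominator.

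Table 1 lists among the exclusion criteria an "Indication for hospital admission due to associated injuries or social/structural reasons". The same table lists mandatory admission grounds, one of which is "Parents feel unsure about going home". Under Observation in the ED, one of the conditions for sending an observed child home is that "adequate medical care in case of emergency must be ensured through a functioning emergency response chain", or alternatively that the guardians can reach the ED.

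Other places that bear on the point:
- Assignment of interventions and blinding: the core team and the local ED staff are not blinded.
- Control group: screening is documented in the eCRF.
- Data collection and management: once the monthly target is met, sites document eligible cases that were not approached. No record of children excluded for an admission indication is described.
- Statistical methods, Clinical evaluation: the intention-to-treat comparison is of patients recruited before and after the switch.

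**The concern.** An exclusion phrased as an indication for admission sits very close to the outcome. Suppose a family has poor access to emergency care or is reluctant to take the child home. The child may be judged ineligible on social or structural grounds and disappear from the first co-primary. Or the child may be included, not discharged, and counted as an event. The article draws no line between these two routes and does not say when eligibility is settled relative to the admission decision.

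The decision lies with staff who know the phase. The phases also differ in structure: the observation period and its discharge conditions exist only under the new pathway. If the line falls in the same place in both phases, little harm follows. If it shifts with the phase, the relative risk shifts with it. Intention to treat and the site and time effects cannot repair this, because they act only on children already counted as recruited. Without a log of these exclusions, the analysts could not reconstruct the loss afterwards.

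**Working it through.** **Inputs from the article** (Sample size calculation; Statistical methods): control risk 50%, target relative risk 0.8 (so 40%), ICC 0.15, 11 sites, 12 months with one site switching per month, 10 children per site per month (1320 in total), two-sided alpha 0.05, fixed effects for intervention and time, random site effects.

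**Assumption:** a share f of would-be admissions is classed as excluded in one phase only. The article gives no figure for f; 5, 10 and 20% are shown. At 50% risk these equal 2.5, 5 and 10% of all children in that phase.

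**Plan's own figure.** A stepped-wedge random-intercept calculation on the log scale, using the control-rate variance and no period effects, gives power 0.886 with 7 and 0.922 with 8 children per site-month. The smallest sufficient size is 8, and 11 × 12 × 8 = 1056, the stated number for this outcome. That match needs the period effects left out, which is a separate matter. The results below keep them in, as the analysis plans.

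**Exclusion in the intervention phase only, no true effect.** Observed risk = p(1 − f)/(1 − pf), with p = 0.5. The probability of a significant result favouring the new pathway is Φ(shift/SE − 1.96). The SE comes from the stepped-wedge model on the risk-difference scale, used as an approximation to the planned log-link model.

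| f | Observed risk | RR | Shift (points) | SE (points) | False claim of reduction |
|---|---|---|---|---|---|
| 5% | 0.475/0.975 = 48.7% | 0.97 | 1.28 | 4.35 | 4.8% |
| 10% | 0.450/0.950 = 47.4% | 0.95 | 2.63 | 4.34 | 8.8% |
| 20% | 0.400/0.900 = 44.4% | 0.89 | 5.56 | 4.33 | 25% |

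The nominal value in that direction is 2.5%. Without period effects the last column would read 6.3, 14 and 47%.

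**Exclusion in the control phase only, true RR 0.80.** With f = 20% the control risk appears as 44.4%, and 40/44.4 = 0.90. A real effect would look half as large.

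**Does the proposed sensitivity analysis recover the truth?** Take 100 children with 50 would-be admissions and f = 20%: 10 are excluded, leaving 40/90 = 44.4%. Counting the 10 as hospitalized restores 50/100 = 50%. This works only if the exclusions were logged.

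**The case against.** The strongest reply is that checking social circumstances at entry and confirming emergency access at discharge are compatible steps, and that in the intervention phase inclusion seems to come first. Study information is given at triage, the app is handed over on inclusion, and the figure legend on the participant timeline puts the final admission decision at the end of observation. Nothing permits removing a child after enrolment, and deviations are recorded with reasons. The full protocol may fix the moment of eligibility and keep a screening log. All of this is fair. It limits the point to an unstated boundary and cut-off, and it makes phase-dependent classification a possibility only. It does not supply the boundary, and it says nothing about the order of events in the control phase.

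Three stronger readings are tempting, and the text does not support them.
- *The same conditions both exclude and admit.* They overlap; they are not identical. Associated injuries, the other half of the exclusion, have no counterpart in the admission list.
- *The device and app rules contradict each other.* "A suitable device is available for the legal guardians to use the parent app" is a fact known before enrolment. That the parents' "app does not work on the smartphone" can emerge only after inclusion, because the app is issued then. An admission on that ground is a consequence of the pathway and counts as such.
- *Most of these conditions become known only at disposition, or worsening under observation makes a child ineligible.* The article does not say the first. As to the second, no inclusion or exclusion criterion in Table 1 uses the monitoring course. The text above the table does base the chosen clinical factors on symptoms "as well as the clinical course during the monitoring period", which is loose wording, but in Table 1 that course appears only as an admission ground ("Newly emerged pathological findings during monitoring in the ED").

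The illustration also assumes that the reclassification is wholly one-sided. That is the extreme case, and no figure in the article supports a particular share.

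**Conclusion.** The point holds in a limited form. One exclusion is defined by an indication for the outcome event. Its social/structural part has no stated boundary with the emergency-access condition for discharge or with parental uncertainty as an admission ground. The article states no time at which eligibility becomes final, and the people deciding are unblinded. The first co-primary could be biased in either direction; nothing shows that it will be.

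The size depends entirely on the assumed share and on that share differing fully between phases. At 5% of would-be admissions the effect is small (RR 0.97, false-claim risk about 5%). At 20% it is material (RR 0.89, about 25%; or a true 0.80 appearing as 0.90). Because trial success requires this outcome and the remedy is cheap, the plan should be clarified.

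**What to change.** 1. State, for both phases, that eligibility, including the social/structural exclusion, is judged on facts recorded at arrival, before the disposition decision, and is not revised afterwards.
2. Count every later admission, for any reason, as an event in the first co-primary.
3. Log each exclusion for an admission indication, by site and phase, in the eCRF screening record.
4. Add a sensitivity analysis of the first co-primary that counts these logged exclusions as hospitalized. It will be conservative, because children rightly excluded in both phases are added too.
5. Reconcile the exclusion with the admission list in Table 1 and the discharge conditions under Observation in the ED, and reconcile the sentence on the clinical course with Table 1. No view is taken on which admission or discharge rule is right.

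The cost is a few sentences of wording and a short arrival checklist and log in both phases. The observed reduction may be slightly smaller, because some admissions that sites might have screened out would now count.

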#### Interventions

The trial is carried out using a cluster-randomized stepped wedge design. The 11 study sites will participate in the study over 12 months. All study sites will start in the control phase and one study site (cluster) per month will switch to the intervention arm, which will be carried out until the end of the study. The switching order will be randomized, and study centers will be informed 8 weeks in advance to switching.

##### Control group

During the control phase, the standard care pathway (sCP) is carried out according to each study site’s current clinical practice, including inpatient or outpatient management. Local standard operating procedures will be collected prior to the beginning of the study. Screening and clinical documentation will be performed using the study’s electronic case report form (eCRF). After 72 h “unplanned re-visits” will be queried via telephone follow-up by the local study team and documented in the electronic case report form (eCRF).

##### Intervention group

The intervention phase is designed to test the nCP, which provides the additional option of secondary outpatient management for low-risk patients after a symptom-oriented observation period in the ED (Fig. 2 and supplementary figure). Upon inclusion during the intervention phase, one of the patients’ caregivers receives a smartphone app designed to facilitate monitoring their child in the home environment.

**Fig. 2 Fig2:**
[figure not shown]
Participant timeline. Inpatient admission and primary outpatient management are available throughout the study and constitute the standard care pathway. After 72 h, follow-up to assess unplanned re-visits and parents’ satisfaction with the treatment is carried out. During the intervention phase, an additional option of a 6-h observation period in the emergency department is added for patients that cannot immediately be discharged from the ED due to their clinical condition. At the end of the observation period, the final decision is made for either inpatient admission or secondary outpatient management. All parents (regardless of inpatient or primary or secondary outpatient management) receive a parent app on their smartphones. In outpatients, the parent app will send push notification to remind parents to assess their child’s condition at pre-specified timepoints (2, 6, 12, 24, and 48 h after presentation to the ED). All parents will receive a push notification to fill out the 72-h follow-up. If the follow-up is not answered via the parent app, parents will receive a phone call by the local study team as in the control phase

##### Observation in the ED

The nCP consists of symptom-based clinical neuromonitoring for at least 6 h starting at ED arrival and includes the assessment of the Glasgow Coma Scale (GCS), pupillomotor function, and vital signs. The frequency and duration of the monitoring and additional measures depend on the patient’s health condition upon arrival at the ED and during monitoring (Table 1). Hospital admission, imaging, or surgery are possible at any time as indicated according to clinical findings and clinical practice guidelines. Patients that remain stable during the nCP will be discharged home if the physician and the legal guardians agree that the child is fully conscious (GCS = 15), behaves age-appropriately, and does not display newly developed symptoms or demonstrates any focal neurological deficits. Pre-existing symptoms, such as headaches or vomiting, must have remained stable (without worsening), show signs of improvement, or have resolved during the monitoring period. The legal guardians must feel confident in conducting home monitoring, and the parent app must function on their smartphone. Additionally, adequate medical care in case of emergency must be ensured through a functioning emergency response chain or by the guardians’ ability to arrive at the ED. Deviations from the recommended care pathway are possible at any time but will be documented along with the reason (Table 2).

**Table 2 Tab2:** Reasons for deviations from the study protocol, including logistical, technical, medical, and personal factors

**Deviations from study protocol**	• Logistical reasons • Technical reasons • Admission at parents’ request • Discharge against medical advice • Study termination by the parents • Medical concerns from the physician • Others (string)

